## Background

Since December 2019, some patients with pneumonitis infected by a new type of coronavirus called COVID-19 were successively found in Wuhan, which raised intense attention worldwide [1]. COVID-19 is a novel type of coronavirus belonging to the family beta-coronavirus, and its gene sequence is significantly different from previous viruses [2]. COVID-19 is mainly transmitted through respiratory droplets and contact and has high infectiousness. Though the authorities gave the highest priority to prompt prevention and treatment of COVID-19, cases of human-to-human transmission are gradually expanding domestically and abroad. As of 27 May 2020, more than 5,406,282 people have been infected, and more than 343,562 deaths have occurred globally [3]. Patients often develop dyspnea or hypoxemia 1 week after the onset of symptoms, and in severe cases, they progress rapidly to acute respiratory distress syndrome, septic shock, etc. [4]. An early study proved that due to a shortage of medical resources, the mortality rate of patients with severe pneumonia is as high as 61.5% [5]. Eventually, the National Diagnostic and Treatment Protocol for Novel Coronavirus Pneumonia (the 7th trial version) was developed to reduce mortality and reinfection [6]. However, more options should be explored to cope with this event [6, 7]. Acupressure is a low-risk physical therapy that is different from acupuncture and is a part of traditional Chinese medicine (TCM). Previous research has shown that acupressure can improve patients’ symptoms of dyspnea in lung diseases and their quality of life [8, 9]. Acupressure is a noninvasive treatment accepted by patients; this treatment is characterized by pressing on acupoints with the hands to achieve clinical efficacy. In addition, Liu Zi Jue Qigong exercises have also been widely used in lung rehabilitation training; these exercises not only relieve symptoms of breathlessness but also have benefits on mental illness [10–12]. Liu Zi Jue Qigong is applicable for the patients with COVID-19 who widely suffer panic and anxiety due to the mortality and infectivity of the disease [13]. These exercises adopt a combination of abdominal breathing and lip breathing to produce six different sounds (xu, he, hu, si, chui, and xi) accompanied by low-intensity body movements [12]. This breathing pattern can change the rapid shallow breathing pattern of lung dysfunction, extend the opening time of the trachea, and maintain the airway pressure of the patient within a physiological range, thereby improving gas exchange [14, 15]. Regarding COVID-19 patients, dyspnea is the most obvious clinical symptom. Furthermore, sudden illness and fear of disease are psychological disorders that each patient will have. Previous studies have shown that acupressure and Liu Zi Jue exercises can improve the respiratory symptoms of patients with lung disease as well as improve their quality of life and mental health. Therefore, effectively combining the two interventions into a rehabilitation method can potentially be used in the clinical rehabilitation of COVID-19 patients. Now, we will combine the acupressure therapy with Qigong exercises as a clinical traditional Chinese medicine rehabilitation (TCMR) method for patients with severe pneumonia. Therefore, we hypothesize that official conventional therapy plus TCMR will have better clinical efficacy than single conventional therapy for clinical symptoms, mental health, and quality of life.

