#### Analysis of primary outcome

The primary outcomes will be evaluated at baseline, 6 days after the intervention, and upon discharge based on the intention-to-treat analysis (ITT). The primary endpoint of the trial is the mean change in mMRC Scales from baseline to the discharge day. Baseline covariates included for adjustment were sex, age category, history of cardiopulmonary disease, and body weight category. The whole outcomes scale was also measured at baseline. When the data have a normal distribution, two-way repeated-measures ANOVA will be used as the main analytic method, and a paired sample *t* test will be used between the two intervention groups; if the normal distribution is not met, the Wilcoxon test will be used as an alternative method. Prior to any analysis, any missing data pattern will be investigated and reasons for missing data obtained and summarized where possible. The percentage of missing data is 20%, and we plan to generate 5 imputed datasets, which is the minimum recommended number [28]. The sensitivity analyses were carried out to assess two assumptions about missing data, and data imputation scenarios can potentially influence the primary result [29]. To account for missing data, our primary analyses were conducted on an imputed data set where missing values were generated using multiple imputation by chained equations (MICE) [30].

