##### Safety evaluation

A safety evaluation will be conducted throughout the trial. Although TCMR programs are low risk, the participants are ill with severe pneumonia. When adverse events occur, the researchers will record them in CRFs in detail and analyze whether they are directly related to the rehabilitation program. Regardless of the cause, if the condition suddenly worsens during the trial and is accompanied by severe complications or serious adverse reactions, the trial will be terminated immediately, and prompt medical measures will be taken according to the subject’s condition. The specialist will be prepared to deal with some harm during the study at any time, with treatments including oxygen therapy support, venous access, and reasonable medication to maintain normal vital signs.

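### No rule is stated for in-hospital death, so filling the discharge-day mMRC by MICE can understate harm if deaths differ between arms

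*Protocol article*

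**What the plan says.** The section Analysis of primary outcome fixes the endpoint: "The primary endpoint of the trial is the mean change in mMRC Scales from baseline to the discharge day". The analysis is by intention to treat. On missing data the section says "The percentage of missing data is 20%, and we plan to generate 5 imputed datasets", and that "our primary analyses were conducted on an imputed data set where missing values were generated using multiple imputation by chained equations (MICE". It also promises that "any missing data pattern will be investigated and reasons for missing data obtained and summarized where possible", and adds: "The sensitivity analyses were carried out to assess two assumptions about missing data". Neither assumption is named, and the reasons for missingness are not linked to how values are filled.

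Three other places bear on this. Dropout and suspension criteria excludes any subject whose hospital stay is shorter than 7 days, because the outcome cannot then be assessed. Safety evaluation says that "if the condition suddenly worsens during the trial and is accompanied by severe complications or serious adverse reactions, the trial will be terminated immediately", and gives no outcome value for such a patient. Analysis of secondary outcomes compares adverse events separately. No section says how a death in hospital enters the primary endpoint.

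**The concern.** A missed assessment and a death are different things. A surviving patient whose discharge form was not completed had a grade that could have been recorded. A patient who died in hospital had no discharge day, so there is no unobserved grade to recover. Every observed discharge grade comes from someone well enough to leave, and those patients are the only source from which the imputation model learns. Under the stated rule, a patient who died receives a modelled grade typical of discharged patients with similar covariates.

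If deaths are equally frequent in both arms, this largely cancels. If one arm has more, the primary comparison loses part of that difference, and loses it in favour of the arm with more deaths. The exclusion of short stays does the same to deaths in the first week and also conflicts with the intention-to-treat statement.

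**Working it through.** **The plan's own figures.** Sample size calculation gives means 0.52 and 0.95 and SDs 0.11 and 0.92, with alpha 0.05 and beta 0.10. The planned difference is 0.95 − 0.52 = 0.43. A two-sided unequal-variance t test at 90% power needs 51 per group, and 51/0.80 = 63.75, rounded up to 64. The stated 64 per group is reproduced, so 0.43 is a fair yardstick. Its direction is not used here.

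**Assumptions (none of these figures is in the documents).** Baseline mMRC is 1, 2, 3 or 4 with probabilities 0.1, 0.3, 0.4 and 0.2, so the mean is 0.1 + 0.6 + 1.2 + 0.8 = 2.7. Survivors follow the same course in both arms and improve by about 1.77 grades by discharge. Patients who later die are about half a grade worse at day 7. Deaths are 5% in control and 15% in treatment; with 64 per group that is 64 × 0.05 = 3.2 and 64 × 0.15 = 9.6 patients.

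**Check.** In a simulation with 200,000 patients per arm, the missing discharge grades were imputed within arm by regression on baseline, with or without the day-7 score. This is the missing-at-random principle behind MICE. The comparator sets death to grade 4.

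| Handling of deaths | Mean change given to a patient who died | Treatment minus control |
|---|---|---|
| Imputed, no day-7 score in model | about −1.8 | 0.00 |
| Imputed, worsened day-7 score in model | about −0.7 | 0.11 |
| Set to grade 4 | 4 − 2.7 = +1.3 | 0.31 |

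Negative change is improvement; a positive arm difference means treatment is worse.

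**Hand check.** Arm difference = (change given to a death − change in survivors) × difference in death proportion.
- Grade 4: (1.3 + 1.77) × 0.10 = 0.307.
- Imputed with day 7: (−0.73 + 1.77) × 0.10 = 0.104.
- Imputed without day 7: about 0.

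**Amount hidden.** With day 7: 0.31 − 0.11 = 0.20, and 0.20/0.43 = 47%. Without day 7: 0.31 − 0.00 = 0.31, and 0.31/0.43 = 72%.

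**Range.** Deaths of 10% and 20% give the same three arm differences (0.00, 0.11, 0.31), because only the 10-point gap matters. A 5-point gap hides about half as much: 2.03 × 0.05 = 0.10 to 3.07 × 0.05 = 0.15. Equal deaths of 5% in each arm give about 0 under every method.

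**Deaths before day 7.** Exclusion leaves only survivors, whose mean change is the same in both arms here. It therefore hides the full 0.31, the same as imputation without a day-7 score.

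**The case against.** The strongest reply is that the article never says a death is to be imputed. That reading comes from its silence, and an analysis plan that is not shown may treat death separately. The silence is real. But the article itself names the primary missing-data method and states no exception, and following it as written produces the result above. The promised summary of reasons and the two unnamed sensitivity assumptions leave room for a remedy without supplying one.

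Several stronger readings are tempting and are not supported:

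- A reader might infer that anyone who deteriorates lacks a discharge mMRC. A patient who worsens or goes to intensive care and later goes home can still be assessed. Safety evaluation does not say that assessment stops.
- A reader might infer that harm is simply scored as recovery. That is the extreme case. Patients still in hospital at day 7 are due an mMRC then, and a poor score in the model cuts the credited improvement from about 1.8 to about 0.7 grades.
- A reader might take the Background statement that "the mortality rate of patients with severe pneumonia is as high as 61.5" per cent as a forecast. It comes from an early study under a shortage of medical resources. This trial enrols stable patients and excludes those on mechanical ventilation or needing intensive care.
- A reader might infer that the bias could outweigh the treatment effect. Even with every death imputed at about 0.75 (near the midpoint of the planning means), the gap per death is 4 − 0.75 = 3.25, so hiding 0.43 needs an imbalance of 0.43/3.25 = 13 points. The 20% in the plan is loss to follow-up or missing data, not deaths.
- The choice that "we plan to generate 5 imputed datasets, which is the minimum recommended number" might look like part of the problem. It is minor: at a fraction of missing information of 0.2, relative efficiency is 1/(1 + 0.2/5) = 0.962 with 5 imputations and 1/(1 + 0.2/20) = 0.990 with 20.

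It is also fair to say that deaths would not go unseen, since adverse events are recorded and compared. That does not correct the primary estimate.

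**Conclusion.** The concern holds in a limited form. As written, the primary analysis has no rule for in-hospital death: later deaths become missing values predicted from discharged patients, and deaths before day 7 are excluded despite intention to treat. If deaths are unbalanced, the comparison can understate harm. With a 10-point imbalance the hidden amount is about 0.2 to 0.3 grade, or 47% to 72% of the planned 0.43. It shrinks in proportion to the imbalance and is about zero if deaths are balanced.

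The size rests on assumed death rates, baseline grades and recovery, and on grade 4 as the value for death. The documents give no event rate for this population, so the direction is firmer than the amount.

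**What to change.** Amend the analysis section as follows.

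1. Keep all randomised patients in the intention-to-treat analysis, including those with stays under 7 days.
2. Assign in-hospital death the worst outcome: a rank below grade 4 in a ranked analysis, or grade 4 if the mean is kept. Report deaths by arm.
3. Restrict MICE to survivors with a missed assessment, with baseline and day-7 mMRC in the model.
4. Keep assessing patients who worsen, stop TCMR or are transferred, and use their actual discharge mMRC. Scoring surviving ventilated or intensive-care patients as grade 4 is not needed; it would overwrite real values.
5. Make one of the two planned sensitivity scenarios a delta-adjusted (not-at-random) imputation.

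The cost is some wording, a few lines of code and continued follow-up of a few patients. The small downside is that the endpoint becomes a composite of dyspnoea and death.

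Separately, the Safety evaluation sentence should be reconciled with itself. Its wording about terminating the trial can be read as ending the whole study, while the rest of the sentence concerns the individual subject.

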#### Analysis of secondary outcomes

Analysis of secondary outcomes will be undertaken using a similar approach to that described for the primary analysis. We will estimate and test for a difference between treatment arms for each endpoint specified in the secondary outcomes listed above. Adverse events will be listed and analyzed using the chi-square test or Fisher’s exact test.

### Interim analysis

#### An interim analysis will not be conducted

##### Quality control

During the whole processing of the trial, quality control will be conducted under the surveillance of the steering committee. To ensure the consistency of methods, all the researchers will be trained with the trial methodology and monitoring technique before participating in the trial. Supervision activities will be divided into online remote monitoring and offline personal inspection every day. If necessary, researchers will be able to submit a request to modify the protocol, such as the primary outcome and sample size calculation. The steering committee and ethics committee will have the authority to allow modification of the plan. In addition, the information will be updated in the clinical registration center in time to ensure that all parties can understand the changes.

##### Safety evaluation

A safety evaluation will be conducted throughout the trial. Although TCMR programs are low risk, the participants are ill with severe pneumonia. When adverse events occur, the researchers will record them in CRFs in detail and analyze whether they are directly related to the rehabilitation program. Regardless of the cause, if the condition suddenly worsens during the trial and is accompanied by severe complications or serious adverse reactions, the trial will be terminated immediately, and prompt medical measures will be taken according to the subject’s condition. The specialist will be prepared to deal with some harm during the study at any time, with treatments including oxygen therapy support, venous access, and reasonable medication to maintain normal vital signs.

## Discussion

The city of Wuhan in China is the focus of global attention due to the outbreak of COVID-19 [31], which has an epidemiological link to the Huanan Seafood Wholesale Market. Although the overall mortality rate is relatively low compared to other coronavirus epidemics [32], the infection has worsened due to encounters from mass migration [33]. Immediate medical measures and rescues by the Chinese Government have been taken to control further deterioration of the epidemic; these include intensive surveillance, epidemiological surveillance, and symptomatic supportive treatment to reduce mortality. Though all the costs of COVID-19 treatment are covered by medical insurance in China, there are still no effective therapies or vaccines except for meticulous supportive care [34]. Therefore, it is necessary to find more measures to deal with this pneumonia. As a category of complementary and alternative medicine, acupressure therapy and Liu Zi Jue Qigong exercises are performed widely in TCM [35, 36]. Some researchers have confirmed that they can improve the clinical symptoms and physical and mental health of patients with lung disease [10, 37, 38]. As the health care system is overloaded, a TCMR program is highly operable and cost-effective [39]. It is a low-risk therapy that does not require large equipment and is not restricted by location or time [40]. Through TCM rehabilitation, the body’s immune system can offset the damage of foreign microorganisms through the dynamic regulation of innate immunity [41]. Previous studies have found that these points can significantly improve lung symptoms, such as cough, chest tightness, and sputum [42]. In addition, Liu Zi Jue Qigong breathing exercises can help restore the physiology of the lungs to diffuse and sink (inhale and exhale). This technique is a pursed-lip breathing and inspiratory muscle training method that can increase muscle strength and respiratory muscle endurance to relieve dyspnea. During the performance of the low-intensity exercise, patients are focused on themselves, which can relieve some anxiety and tension attributed to a negative situation [43]. According to the TCM macro theory, the TCMR program can harmonize qi and blood coordination and regulate the balance of yin and yang. However, more strong evidence is necessary to further prove the efficacy of TCMR programs for improving the symptoms and prognosis of patients with COVID-19. Therefore, this clinical trial was conducted to evaluate the efficacy of a TCMR program including acupressure and Liu Zi Jue Qigong exercises to improve pneumonia and quality of life of patients with COVID-19.

### Trial status

This trial is recruiting patients now. Participant recruitment started on 20 February 2020 and is expected to end on 30 June 2020. This trial was registered in the Chinese Clinical Trial Registry on 18 February 2020. The registration number is ChiCTR2000029994.

Protocol version 3, 8 July 2020.

## Data Availability

The protocol manuscript does not contain any data, so we declare that data and materials are not applicable in this study. The datasets generated and analyzed during the study will be available in the Figshare repository.

## Abbreviations

COVID-19: Novel coronavirus pneumonia
ADL: Activities of daily living
CRF: Case report form
mMRC: Modified Medical Research Council
PHQ-9: Patient Health Questionnaire-9
SUTCM: Shanghai University of Traditional Chinese Medicine
RS: Respiratory symptoms
TCMR: Traditional Chinese medicine rehabilitation
